5.1 Primary outcome measurements

Clinical cure (short and long term): clinical symptoms (pain and burning sensation rating), signs (pseudomenbran and erythema grade)

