5.2 Secondary outcome measurements

• Clinical improvement rate: (score of symptom and clinical sign at baseline- score of symptom and clinical sign post treatment)/ score of symptom and clinical sign at baseline

• Mycological: Eradication of organism (negative culture and negative microscopy)*

• Safety: Number of patient withdrawals due to adverse reactions; Incidence of adverse reactions (reported as side-effects).

*Candida albicans is found routinely in asymptomatic population, therefore, it would have been inappropriate to use mycological eradication as the primary outcome measure for the study.

The cure is defined as complete clinical response and eradication of Candida spp. at Day 7 or Day 14. A complete clinical response was defined as the complete disappearance of oral candidiasis lesions, and a partial clinical response was defined as ≥60% of clinical improvement rate compared with the score at baseline. <60% of clinical improvement rate and candida persistence, re-infection or species shifts were considered failures. Finally, biologic, local, and general safety was compared between treatments.

Participants will also be required to complete their daily diaries from the start of the treatment period until the end of the treatment period. Blood tests for full blood count and liver and kidney function tests will be conducted at initial assessment and during the final clinic visit (week 4).

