8.3 Research process

Potential participants will undergo preliminary screening for eligibility during visit 1 by investigators, which will include a registered oral medicine specialist. Eligible participants will then undergo initial assessments for review of system (ROS), baseline data collection, which include the symptom scoring, grade of clinical sign of oral candidiasis, measurement of vital signs (temperature, blood pressure and heart rate. ECG), full blood count, kidney function test and liver function test. The candida-related laboratory testing (smear test and fungi culture) will be performed to gather the baseline data of candida infection and colony forming unit count. A daily diary will then be given to record the change of symptoms and occurrence of adverse events and use of topical treatments during the 2-week treatment period. After signing the consent form, participants will be randomly assigned to either the treatment (miconazole mucoadhesive tablet) group or the control (itroconazole capsule) group and the treatment period will start. During this clinic visits, participants will be given 1 weeks’ worth of miconazole mucoadhesive tablet or itroconazole capsules and daily diaries for the fortnight.

In visit 2 of 1week after, the participants will be re-evaluated on the symptom scoring, grade of clinical sign, vital signs, smear test and fungi culture). The participants will repeat 1-week treatment and record the daily diary during the following week. In visit 3 (the following day after the 2-week treatment period) and visit 4 (2-week follow up after treatment ceasing), the participant will be evaluated by performing clinical and laboratory examination as baseline.

Throughout the treatment period, other medication or therapies, such as anti-hypertension drugs, is allowed to be used on an ‘as needed’ basis. During this treatment period, participants will also be required to record their medication intake, including trial interventions, other medications intake and occurrence of adverse events to assist with compliance monitoring and acceptability of intervention. Participants will be asked to return their medication pack to enable the counting of left-overs as well as part of participant adherence monitoring.

[figure not shown]

Figure 2. Outline of trial protocol

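### The only definition of cure accepts Day 7 or Day 14, overlaps with the failure rule, and gives no rule for the long-term cure that Section 5.1 makes primary

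*Protocol*

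**What the plan says.** Section 5.1 of the protocol gives the primary outcome as "Clinical cure (short and long term): clinical symptoms (pain and burning sensation rating), signs (pseudomenbran and erythema grade". It attaches no day to either the short or the long term.

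Section 5.2, on secondary outcomes, holds the only definition of cure: "The cure is defined as complete clinical response and eradication of Candida spp. at Day 7 or Day 14". It continues: "A complete clinical response was defined as the complete disappearance of oral candidiasis lesions". That component has no day of its own. The same paragraph then defines failure: "<60% of clinical improvement rate and candida persistence, re-infection or species shifts were considered failures". No time window is given, and nothing says which label prevails if a patient meets both definitions. A footnote in 5.2 explains that mycological eradication would be unsuitable as the primary measure, because Candida is common in people without symptoms.

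Section 8.3 sets the visits. At one week (visit 2), symptoms, signs, smear and culture are all assessed again. Visit 3 is the day after the two-week treatment period. The last is "visit 4 (2-week follow up after treatment ceasing), the participant will be evaluated by performing clinical and laboratory examination as baseline".

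**The concern.** A binary primary endpoint must put each patient in exactly one class at a named time. Here three things do not fit together.

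- **Either-visit wording.** Taken at face value, clearance at Day 7 is enough, whatever is found at Day 14.
- **Overlap with failure.** The failure sentence covers re-infection, so a patient who clears and then relapses can meet both definitions.
- **No long-term rule.** The cure sentence stops at Day 14. The follow-up visit, the only one well after treatment ends, enters no definition of cure, yet long-term cure is part of the primary outcome.

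The components differ as well. Section 5.1 rests clinical cure on symptoms and signs, while cure in 5.2 also requires eradication, which the footnote rejects as the primary measure. The opening of Section 5 nevertheless lists Candida elimination among the primary measures.

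Section 11.2 adopts a non-inferiority approach, and Section 3.4 leaves investigators and outcome assessors unblinded. Room to choose the visit or the label after the data are seen is therefore a real weakness.

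**Working it through.** **1. The rules applied to visit patterns.** Clear means lesions gone and Candida eradicated.

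| Day 7 (visit 2) | Day 14 (visit 3) | Visit 4 | Cure sentence, literal reading | Failure sentence | Long-term cure |
| --- | --- | --- | --- | --- | --- |
| clear | clear | clear | cured | no | no rule |
| not clear | clear | clear | cured | no | no rule |
| clear | relapsed | any | cured | failure (re-infection) | no rule |
| clear | clear | relapsed | cured | failure (re-infection) | no rule |

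Rows 3 and 4 carry both labels. If the failure sentence is taken to need improvement below 60% together with a mycological finding, fewer relapsed patients are failures. Those who meet both conditions after an earlier clearance still carry both labels.

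**2. The plan's own figure.** Section 3.2 gives an 85% efficacy rate, one-sided alpha 5%, power 80% and 158 per group. No margin is stated. With margin d and equal true rates,

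n = (1.645 + 0.842)² × 2 × 0.85 × 0.15 / d².

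At d = 0.10 this is 6.183 × 0.255 / 0.01 = 157.7, so 158. Margins of 9 and 11 points give 195 and 131. The 10-point margin is therefore back-solved. The 85% is not tied to a visit, so the sample size does not settle which definition was meant.

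**3. Effect on the cure level (assumed inputs).** The protocol gives no Day-7 cure rate and no relapse rate. Compared with cure at Day 14 alone, the either-visit reading adds

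P(clear at Day 7) × P(not clear at Day 14, given clear at Day 7).

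- Low end: 0.30 × 0.05 = 0.015, or 1.5 points.
- High end: 0.60 × 0.20 = 0.12, or 12 points.

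**4. Effect on the comparison (assumed inputs).** Take true Day-14 cure of 75% on miconazole and 85% on itraconazole, which is exactly at the back-solved margin, with 158 per arm. Let p be the share clear at Day 7 in both arms. The rates under the either-visit reading are t = 0.75 + p × r(test) and c = 0.85 + p × r(control), where r is relapse by Day 14. The chance of declaring non-inferiority is

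Φ{(t − c + 0.10)/SE − 1.645}, with SE = √{[t(1 − t) + c(1 − c)]/158}.

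| p | Relapse, test / control | t | c | t − c | Chance of declaring non-inferiority |
| --- | --- | --- | --- | --- | --- |
| 0.30 | 10% / 10% | 0.780 | 0.880 | −0.100 | 5% |
| 0.30 | 20% / 5% | 0.810 | 0.865 | −0.055 | 29% |
| 0.60 | 20% / 5% | 0.870 | 0.880 | −0.010 | 78% |
| 0.30 | 5% / 20% | 0.765 | 0.910 | −0.145 | 0.3% |

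Equal absolute inflation leaves the difference unchanged. Unequal relapse moves the result in either direction.

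**The case against.** Several stronger readings are tempting, and the protocol does not support them.

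- **That relapse after Day 7 simply counts as cure.** The failure sentence in the same paragraph names re-infection. The defect is double classification without precedence.
- **That long-term cure cannot be computed.** Visit 4 repeats the clinical and laboratory examination, and complete clinical response is tied to no day. The data will exist; the definition does not.
- **That the added cure points can be set against the margin.** The inflation is in a level, while the margin applies to a difference between arms.
- **That a Day-7 swab shows suppression only in the topical arm.** Both arms are on daily treatment at Day 7, and nothing in the protocol supports an effect in one arm alone.
- **That two primary time points inflate the error rate.** The figure of 1 − 0.95² = 9.75% (independent results; 8.8% at correlation 0.5) applies only if success at either time point suffices. The protocol states no such rule, and requiring both would not inflate the error.

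A fair defence is that the cure wording may mean cure assessed separately at each of the two visits. That would remove the contradiction in the third row of the table. One could also guess that Day 7 is the short term and Day 14 the long term. The text says neither. The separate-visit reading still gives visit 4 no rule, and the guess would leave the follow-up visit unused for cure.

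A further defence is that the cure sentence stands under secondary outcomes and includes eradication, so it may not be the primary endpoint at all. That is possible, but then primary clinical cure has no cure definition of its own. Detail on multiplicity may properly sit in an SAP that is not shown. The conflict between stated definitions is in the protocol itself.

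**Conclusion.** The point holds as a conflict between definitions. The primary outcome includes long-term cure, but no rule defines it at visit 4. The one definition of cure accepts either of two visits up to the end of treatment, and it overlaps with a failure rule that has no window or precedence. Its eradication component does not match the symptoms and signs of Section 5.1. This should be resolved before analysis, because it concerns the primary endpoint of an open-label non-inferiority trial.

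The documents do not give the size of the effect. The 1.5 to 12 points added to the cure level rest on assumed Day-7 clearance of 30–60% and relapse of 5–20%. The shift in the chance of declaring non-inferiority, from 5% to 29% or 78% in one direction and to 0.3% in the other, also assumes the back-solved 10-point margin and relapse that differs between arms. These figures show that the wording could decide the result. They do not show that it favours either drug.

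**What to change.** In Sections 5.1 and 5.2:

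1. Delete the either-visit rule. Define short-term cure at visit 3 (end of treatment) only, and long-term cure as cured at visit 3 and still cured at visit 4.
2. State that relapse or re-infection by the visit in question overrides any earlier clearance.
3. Report Day 7 descriptively.
4. State which time point decides non-inferiority. For example, test short-term cure first and long-term cure only if it succeeds, or require both.
5. Reconcile the eradication component with Section 5.1 and the 5.2 footnote, so that primary clinical cure rests on symptoms and signs and eradication stays secondary. Align the opening of Section 5 accordingly.

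The cost is wording only. All visits and tests are already scheduled. The reported cure rate may be somewhat lower than under the either-visit reading.

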5.3 Safety monitoring

A blood sample will be obtained at baseline（day -3~0）, endpoint of 2-week treatment (day 14+1), 2-week follow-up visit （If the patient reported an abnormal blood result at 3rd visit, then additional blood test would be required in the 4th visit）. A full blood examination, assess liver and renal function. For the duration of the trial, the principal investigator will be contactable by telephone at all times. Any adverse medical events reported by the patient will be recorded in the patients’ medical records at each visit. All adverse events will be followed up from the date it is brought to the investigator’s attention until the adverse event has been resolved. In the occasion of a severe adverse event occurring after initiation of the trial, the event will be recorded and immediately reported to the SFDA, followed by a detailed written report. Participants will be identified by their ID codes to maintain confidentiality. Participants may be withdrawn from the trial by the investigator if a serious adverse event occurs.

**6. Trial discontinuation or modification**

The participants will be able to end participation or withdraw consent at their own request at any time. Participants will be withdrawn from the trial if they suffer from an unexpected serious adverse event.

Under some circumstances, certain modifications to the manufacturing changes, and/or to the clinical protocol during the course of the clinical investigation can be made. Any such changes will be required to report to IRB for approval.

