9.4 Abnormal laboratory results

The investigator should judge whether the abnormal laboratory results are of clinical significance and provide possible interpretation. The reported adverse event which causes the abnormal laboratory results should also be recorded as adverse events in ADR.

- 9.5 Follow-up and adverse event record

Adverse events, especially the events which have a connection with the investigational drugs, should be followed up until they return to the baseline or tend to be steady. If follow-up can’t make the adverse events back to the baseline or to be steady, then it should be recorded and explained in the CRF. Any serious adverse events occurred in the clinical trial must be reported to the sponsor and major research institution within 24 hours. At the same time, the investigator must fill in the SAR report and record the  occurrence time, seriousness, duration, measurement and turnover.

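### Section 6 withdraws a patient with an unexpected serious adverse event from the trial rather than from study drug, so the remaining scheduled visits and blood tests are not guaranteed

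*Protocol*

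**What the plan says.** Two sections govern exit after a serious adverse event.

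- Section 6 is mandatory for unexpected serious events: "Participants will be withdrawn from the trial if they suffer from an unexpected serious adverse event".
- Section 5.3 is discretionary for any serious event: "Participants may be withdrawn from the trial by the investigator if a serious adverse event occurs".

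Section 6.1 describes withdrawal by the researcher as leaving the research process. Section 6.2 allows the last available result to stand as final for a patient who withdraws for whatever reason. Section 11.1 fills missing efficacy evaluations by LOCF.

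Follow-up of the event continues. Under 5.3 it runs "until the adverse event has been resolved". Under 9.5 adverse events "should be followed up until they return to the baseline or tend to be steady".

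The visit content is in 8.3. At visit 2, "the participants will be re-evaluated on the symptom scoring, grade of clinical sign, vital signs, smear test and fungi culture". At visits 3 and 4, "the participant will be evaluated by performing clinical and laboratory examination as baseline". Section 5.2 says that the blood tests "will be conducted at initial assessment and during the final clinic visit (week 4"). Section 5.3 places them at baseline and at the end of treatment, with a repeat at visit 4 if the visit-3 result was abnormal.

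**The concern.** Stopping study drug and leaving the trial are different decisions. The first protects the patient. The second also ends scheduled data collection, and it does so in the patients whose safety data matter most. The protocol uses one term, withdrawal from the trial, for both.

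Blood count and liver and kidney function are among the protocol's named safety indices. If a patient leaves during treatment, nothing in the protocol ensures that these are measured again. On the efficacy side, 5.1 lists clinical cure in the short and the long term as primary. Visit 4 is the only visit after the end-of-treatment assessment, so it is the natural source of the long-term result. For a withdrawn patient that result would be carried forward instead of observed.

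**Working it through.** The protocol gives no figure for this point to reproduce, so the check is a reading of the schedule followed by a rough size.

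**1. Visit days.** Visit 2 is one week after the start: day 7. Visit 3 is the day after two weeks of treatment (8.3; 5.3 gives 14+1): day 15. Visit 4 is two weeks after treatment ends: 14 + 14 = day 28.

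**2. First routine post-baseline blood test.** The three sections that set the schedule differ, so each is read separately.

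| Section | Post-baseline blood tests |
| --- | --- |
| 5.2 | Week 4 |
| 5.3 | Day 14+1; repeated at visit 4 if abnormal at visit 3 |
| 8.3 | Visits 3 and 4, as at baseline; none listed at visit 2 |

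On every reading, no scheduled blood test falls between baseline and day 14. A patient who leaves before then has no guaranteed routine result. For a patient who leaves after visit 3, the answer depends on the section: under 5.3 a normal visit-3 result means that no further test was due.

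**3. Provision for withdrawn patients.** Sections 5.3, 6, 6.1, 6.2, 8.3, 9.5 and 11.1 were compared. They provide for follow-up of the event and for use of the last result. None of them keeps a withdrawn patient on visits 2 to 4.

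**4. Patients affected.** The total is 380 (3.2). The withdrawal rate is assumed to be 0.1% to 2%.

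- 380 × 0.001 = 0.38
- 380 × 0.02 = 7.6

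**5. Of these, patients leaving before the visit-3 blood test.** If events fall evenly over 28 days (a second assumption), the share is 15/28 = 0.536.

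- 0.38 × 0.536 = 0.20
- 7.6 × 0.536 = 4.07

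So 0.2 to 4.1 patients would have no guaranteed routine post-baseline blood result.

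**6. Effect on efficacy.** The carry-forward to visit 4 spans 28 − 7 = 21 days from visit 2, or 28 − 15 = 13 days from visit 3. One wrongly carried result moves one arm's long-term cure rate by 1/190 = 0.53 points with all randomised patients analysed, or 1/158 = 0.63 points with the 158 per group that 3.2 requires before the dropout allowance. If the withdrawal rate is the same in both arms, the most that one arm can move is the rate itself (0.1 to 2 points). That ceiling is reached only if every carried value is wrong in the same direction. Errors of the same kind in the other arm would offset it in the comparison.

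**The case against.** The strongest case against is that a patient with a serious event is under active follow-up. Sections 5.3 and 9.5 require the event to be followed, and 9.4 has the investigator judge abnormal laboratory results. Clinically relevant blood tests may well be done, and no text forbids later visits. The main safety outcomes in 5.2, adverse reactions and withdrawals due to them, are captured by the event itself, and 11.2 keeps everyone with at least one dose in the safety analyses. The eligibility criteria remove many high-risk patients, treatment lasts two weeks, and the mandatory rule covers only unexpected events.

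Most of this stands. It limits the point to the scheduled blood panel and visits, which are not guaranteed, and it makes 2% look generous. It does not supply a rule that keeps those visits.

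A reader might go further in four ways that the protocol does not support:

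- *The blood results are certainly lost.* Event follow-up may produce some. The protocol only fails to require the scheduled ones.
- *Patients who leave before visit 2 fall outside the FAS.* Section 11.1 asks for one evaluation after medication and does not say that it must be at a scheduled visit. An evaluation when the event occurs could qualify.
- *The drug stop goes unrecorded, because the 9.1 category that covers drug withdrawal sets severe events apart.* Serious events have their own 24-hour report under 9.5, 6.2 asks for the reason for withdrawal, and 7.2 and 7.5 record drug use and returns.
- *Sections 5.3 and 6 contradict each other.* They can be read as two tiers: mandatory for unexpected serious events, discretionary for the rest.

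**Conclusion.** The point holds as a minor one, with moderate confidence. The wording of 5.3 and 6 ties a safety-driven drug stop to departure from the trial, and no section restores the remaining visits. A patient who leaves before day 14 is not guaranteed a routine post-baseline blood count, liver or kidney result. The visit-4 result is filled by the last observation.

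The size is small: 0.4 to 7.6 of 380 patients, of whom 0.2 to 4.1 would leave before the visit-3 blood test. Both ranges rest on an assumed withdrawal rate, and the second also on even timing, because the protocol gives neither. The effect on the efficacy comparison is negligible. Cure as defined in 5.2 is assessed at Day 7 or Day 14, so the short-term result is little affected. The case for a change rests on safety data.

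**What to change.** Change the wording in two places.

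- Section 6: *Study drug will be stopped after an unexpected serious adverse event.*
- Section 5.3: *The investigator may stop study drug after any serious adverse event.*
- Add to both: *The participant remains in the trial and attends the remaining scheduled visits and blood tests unless consent is withdrawn.*

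Record drug stop and trial exit as separate CRF items, if the CRF (not shown) does not already do so. Note any other antifungal used up to visit 4, because the daily diary ends with the treatment period and later efficacy scores cannot be interpreted without this. Section 6.2 needs no change.

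The cost is a few sentences, at most one CRF item, and a question about antifungals at visits 3 and 4. No patients or visits are added. A few patients will attend scheduled visits while off drug. Their efficacy scores after another antifungal need a handling rule, in the protocol or the SAP: in a non-inferiority comparison, rescued patients scored as observed could make the arms look more alike than they are.

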6.1 Withdraw decided by researcher

Subject withdrew the study indicates that the enrolled subject cannot continue research at certain condition, and researcher decides the subject to withdraw from research process.

6.2 Subject withdraw research voluntarily

According to informed consent, subject has the right to withdraw research; if the subject does not put forward the idea of withdrawing research clearly, but losses to follow up for refusal taking medication or detection, he or she also withdraws researcher (or “off”). The reason of withdraw should be comprehended and recorded.

The history record table should be preserved for the subject who withdraws research for any reasons, the last detection result can be considered as final result, and curative efficacy and adverse effect should take full data set analysis.

